### Study protocol

A flowchart of the study protocol is presented in the Figure. Investigations will be performed in all participants at baseline in controls and within the 6 weeks before nephrectomy in donors, with subsequent follow-up studies performed at 12 months. Kidney donors will undergo routine follow-up by their local medical and surgical team with no alteration to normal care. No restrictions will be made to the introduction of any treatment including antihypertensive drugs. At baseline and follow-up visits, body mass index (BMI), blood pressure, heart rate, and any clinical events will be recorded.

**Figure f0005:**
[figure not shown]
EARNEST study timeline. Abbreviations: ABPM, ambulatory blood pressure monitoring; AIx, augmentation index; BP, blood pressure; CTX, carboxy-terminal collagen cross-links; FeNa, fractional excretion of urinary sodium; Hb, hemoglobin; MRI, magnetic resonance imaging; NT-proBNP, N-terminal prohormone of brain natriuretic peptide; OC, osteocalcin; OPG, osteoprotegerin; PO_4_, phosphate; P1NP, N-terminal propeptides of type I procollagen; RANK-L, receptor activator of nuclear factor κB ligand.

Table II summarizes the main outcome variables of interest and the relevant data collection methods. Office blood pressure will be measured on 3 occasions using a validated automated device. The first measurement will be made after at least 5 minutes of seated rest. Two further readings will be taken with at least 1 minute between readings. All measurements will be made from the nondominant arm using the same cuff size. Participants will also undergo 24-hour ambulatory blood pressure monitoring using a British Hypertension Society validated oscillometric recorder (Mobil-O-Graph NG; IEM, Stolberg, Germany), which will provide data on both peripheral and central blood pressure.^32^, ^33^

**Table II t0010:** Summary of EARNEST outcome variables and data collection methods

Outcome	Method
Primary outcomes	
Aortic stiffness (aPWV)	aPWV (SphygmoCor; AtCor Medical) will be performed after 15 min of supine rest using a high-fidelity micromanometer (SPC-301; Millar Instruments), as previously described.^34^ Path length is taken as sternal notch-to-femoral pulse distance minus sternal notch-to-carotid pulse distance.
Mean 24-h ambulatory peripheral and central systolic blood pressure	Mean systolic blood pressure from the nondominant arm using a 24-h monitoring system (Mobil-O-Graph NG; IEM). Readings taken every 30 min during the day (0800-2200) and every 60 min overnight
Secondary outcomes	
Office systolic and diastolic blood pressure	Three separate measurements taken after at least 5 min of seated rest using a BHS validated automated device, mean of last 2 recorded
Other ambulatory blood pressure parameters	Mean 24 h and daytime systolic and diastolic blood pressure, pulse pressure
New-onset hypertension	Diagnosis is defined as new antihypertensive therapy and/or systolic blood pressure >135 mm Hg or diastolic blood pressure >85 mm Hg during the daytime on 24-h ambulatory monitoring.
Augmentation index and central hemodynamics	A micromanometer (SPC-301; Millar Instruments) will be used to flatten but not occlude the radial artery using gentle pressure. An averaged peripheral waveform and corresponding central waveform will be generated after 11 s of data capture. The central waveform will then be analyzed to determine augmentation index and central aortic pressures.
Renal function	Isotopic GFR using the renal clearance of ^51^Cr-EDTA will be measured in donors.
Bloods	Hemoglobin, creatinine, calcium, albumin, glucose, phosphate, PTH, NT-proBNP, and uric acid
Urine	ACR and fractional excretion of sodium

Abbreviations: *BHS*, British Hypertension Society; *EDTA*, ethylenediaminetetraacetic acid; *NT-proBNP*, N-terminal prohormone of brain natriuretic peptide.

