The mechanisms by which CKD exerts adverse effects on cardiovascular structure and function are diverse and have been the subject of recent reviews.^12^, ^13^ Leading potential mediators include increased arterial stiffness, hypertension, increased left ventricular (LV) mass and abnormal bone mineral metabolism, which may lead to increased vascular calcification.^12^ There is strong cross-sectional evidence that aortic pulse wave velocity (aPWV; a validated measure of arterial stiffness) increases as GFR falls.^14^, ^15^, ^16^ In a community-based study, among treated hypertensive patients, even minimally impaired baseline renal function was associated with an increased rate of aortic stiffening.^17^ Aortic PWV is an independent predictor of all-cause and cardiovascular mortality in many populations including patients on dialysis,^18^, ^19^ and failure to lower aPWV by angiotensin-converting enzyme inhibitors and blood pressure reduction has been associated with reduced survival.^20^ To date, only one study examining arterial stiffness in kidney donors after nephrectomy has been published.^21^ This had a cross-sectional observational design, comparing 101 kidney donors at a mean of 111 ± 42 months from donation with healthy controls matched only for age and gender, indicating that aPWV was significantly higher in donors. In a recent uncontrolled study of 17 donors, although aPWV was not examined, augmentation index and central arterial pressure were unchanged at 6 months compared with baseline.^22^

With respect to the effects of kidney donation on peripheral blood pressure, the data are inconclusive, but the best available evidence from a meta-analysis suggests a moderate increase of about 5 mm Hg in systolic pressure at 10 years after donation.^23^ Although high-quality prospective studies of donors are still required, in the general population, even a 2-mm Hg increase in systolic blood pressure is associated with a long-term increase in mortality of about 10% for stroke and 7% for ischemic heart disease.^24^ Thus, it appears that either the adverse effects of hypertension in kidney donors are small and as yet undetected by clinical end point studies or that regular medical supervision postdonation has allowed early initiation of antihypertensive therapy and thereby prevented harmful sequelae.

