## Discussion

There is strong evidence that patients with CKD have increased cardiovascular risk with a graded relation with both eGFR and the level of albuminuria.^62^ However, previous studies are limited by their cross-sectional and observational nature, and causation has not yet been established. The true impact of CKD on the cardiovascular system remains hard to define because the duration of the CKD is often unknown, the underlying causes are diverse, and there are numerous confounders including associated diseases such as hypertension and diabetes. Moreover, the level of GFR at which adverse structural and functional changes occur within the heart and vasculature and at which cardiovascular risk starts to rise is not clear. Kidney donors provide a unique healthy population who change at a known time point from having normal to impaired renal function. This study should establish whether reduced GFR leads directly to adverse cardiovascular effects such as increased arterial stiffness, hypertension, LV mass, and mineral bone disorder. Because the prevalence of CKD is high and rising (14.0% in the United States in 2005-2010, as defined by eGFR <60 mL/min per 1.72 m^2^ or ACR ≥30 mg/g),^26^ it is important to establish if a causal relationship exists to determine whether targeting CKD alongside more traditional risk factors could lead to reductions in cardiovascular mortality and morbidity. The potential size of this effect is salutary. If causative, it has been estimated that up to 10% of vascular events in middle age and 20% in old age might be attributable to reduced eGFR.^63^

By careful prospective measurement of ambulatory blood pressure in living kidney donors before and after nephrectomy, this study will also provide important practical information needed for patient care. By clarifying whether there is an increased frequency of hypertension and surrogate markers of cardiovascular disease after donation, we will be able to better advise potential donors in future and inform national guidance on the importance of long-term follow-up.

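### New-onset hypertension counts any new antihypertensive therapy as a case while routine follow-up is described only for donors, so closer observation could add donor cases; the two limbs should also be shown separately

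*Protocol article*

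**What the plan says.** Table II lists new-onset hypertension as a secondary outcome: "Diagnosis is defined as new antihypertensive therapy and/or systolic blood pressure >135 mm Hg", or diastolic above 85 mm Hg, in the daytime on 24-hour ambulatory monitoring. Either limb is enough. The row names no indication for the therapy and no study reading to confirm it.

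The Study protocol section states: "Kidney donors will undergo routine follow-up by their local medical and surgical team with no alteration to normal care". It then adds: "No restrictions will be made to the introduction of any treatment including antihypertensive drugs". It describes no corresponding clinical follow-up for controls. According to Study population, controls are people found fit to donate who did not go on to surgery, or relatives of donors.

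The ambulatory limb is scheduled alike for everyone. Investigations take place at baseline, "with subsequent follow-up studies performed at 12 months", and the equipment paragraph says: "Participants will also undergo 24-hour ambulatory blood pressure monitoring".

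Two further places bear on the point. Background and rationale offers two possible explanations for the reassuring outcome studies in donors; one is that "regular medical supervision postdonation has allowed early initiation of antihypertensive therapy". The Discussion gives the practical aim: "By clarifying whether there is an increased frequency of hypertension and surrogate markers of cardiovascular disease after donation", the authors expect to advise future donors better and to inform national guidance on follow-up.

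**The concern.** The outcome joins two limbs of different kinds. The ambulatory limb is a study measurement taken in the same way in both groups. The therapy limb records a clinician's decision, so it depends on how often pressure is checked outside the study and on local prescribing habits. If donors are seen more often than controls, some donors will start a drug for a raised clinic or borderline reading, while a control with the same pressure is not observed and not treated. The donor is a case and the control is not.

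The predictable direction is towards more hypertension in donors. At stake is the yes/no result closest to the question in the Discussion, whether hypertension becomes more frequent after donation. A single merged figure would not show whether a donor excess came from measured pressure or from prescriptions.

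**Working it through.** **Is there a figure in the plan to reproduce?** None for this outcome: the article gives no hypertension rate, effect size or power for it. The only sizing is for the coprimary end points (SD of change 1.0 m/s or 10 mm Hg, difference 0.22 m/s or 2.2 mm Hg, two-sided 2.5%, 80% power). It reproduces: n per group = 2 × (2.241 + 0.842)² × (1.0/0.22)² ≈ 393, against 400 stated, and 400/0.91 ≈ 440 recruited. The point does not depend on it; 400 per group is used below only as a scale.

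**Who can be miscounted?** Take four kinds of participant at 12 months:

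1. Untreated, ambulatory pressure above threshold: a case in either group.
2. Treated, still above threshold: a case in either group.
3. Treated and now below threshold, but would be above it untreated: a case through the therapy limb. An unobserved counterpart in the other group is a case through the ambulatory limb. The composite handles this correctly.
4. Treated, and would be below threshold even untreated (clinic-only or borderline readings, or a drug given for another reason): a case. An unobserved counterpart is not a case.

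Only the fourth kind creates a difference without a difference in blood pressure.

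**How large could it be?** Let p be the proportion above the ambulatory threshold, equal in both groups; c the proportion of therapy-only cases among controls; x the extra proportion among donors. With no true effect,

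risk ratio = (p + c + x) / (p + c).

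All values of p, c and x are assumptions. With c = 0, and with the chance of a significant donor excess taken from a two-sided 5% comparison of proportions with 400 per group:

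| p | x | Risk ratio | Chance of a significant excess |
|---|---|---|---|
| 3% | 1% to 5% | 4/3 = 1.33 to 8/3 = 2.67 | 12% to 88% |
| 5% | 1% | 6/5 = 1.20 | 9% |
| 5% | 2% | 7/5 = 1.40 | 22% |
| 5% | 5% | 10/5 = 2.00 | 77% |
| 10% | 1% to 5% | 11/10 = 1.10 to 15/10 = 1.50 | 7% to 57% |

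If controls also have therapy-only cases the ratio shrinks. With p = 5% and c = 2%, x from 1% to 5% gives 8/7 = 1.14 to 12/7 = 1.71. The article states no test for this outcome, so the last column is illustrative only.

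**Would the ambulatory limb alone do?** Suppose 5% in each group would be above threshold untreated, and earlier treatment brings 2% of all donors from above to below it. The ambulatory limb alone gives 3/5 = 0.60, a spurious benefit of donation. The composite gives 5/5 = 1.00. Each version fails in a different direction.

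**The case against.** The strongest reply is that the composite is the conventional safeguard against treatment hiding hypertension, and that ambulatory monitoring of everyone at 12 months already finds the untreated hypertensive control. Both parts are right. They confine the problem to the fourth group above and rule out replacing the composite with the ambulatory limb. They do not remove the fourth group.

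A reader might infer more than the document supports:

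- **That controls have no medical care beyond the two study visits.** The article is silent on controls' ordinary care. CRIB-DONOR participants also have office and ambulatory pressure measured at 6 months.
- **That the authors concede supervision leads to treatment.** Background and rationale offers it as one of two alternatives, the other being that the adverse effects are small.
- **That a false excess is bound to appear.** No rates are given, and the ratios above only restate the assumed gap.
- **That disease and detection are wholly inseparable.** Daytime ambulatory pressure is a secondary outcome in its own right, and antihypertensive use is a covariate in the coprimary model, so the limbs can be tabulated. What the stated definition lacks is the reason for the prescription.
- **That the advice to donors rests on this composite.** The Discussion ties that aim to ambulatory measurement, and the coprimary ambulatory systolic pressure is not inflated in this way.

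It can also be said that the word diagnosis implies treatment for hypertension, and that the entry exclusions in Table I (diabetes, atrial fibrillation, LV dysfunction, significant proteinuria) leave few other indications. That makes non-pressure prescriptions less likely. It does not touch prescriptions prompted by closer observation.

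**Conclusion.** The point holds in a limited form. As defined, the outcome lets unequal observation enter the donor-control comparison through cases with new therapy and ambulatory pressure below threshold, and the likely direction is against donation. It affects one secondary outcome.

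The size is unknown. The central illustration, a risk ratio of 1.2-2.0 with no true effect, rests on three assumptions: 5% of each group above the ambulatory threshold, no therapy-only cases among controls, and 1-5% of donors being therapy-only cases. A higher base rate, or some therapy-only cases among controls, brings it nearer to 1. Table I admits people taking up to two antihypertensives, so the number at risk of new onset may be below 400 per group and the chances of significance shown are approximate. The change is worth making because it is cheap and because the reason for a prescription, if not recorded at the time, is hard to recover later.

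**What to change.** In Table II and the analysis of this outcome:

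1. Keep the composite. Beside it, report by group (a) daytime ambulatory pressure above threshold, whatever the treatment, and (b) new therapy with ambulatory pressure below threshold. These do not overlap and together make up the composite, so its donor-control difference is the sum of the differences in (a) and (b).
2. At 12 months, record drug, start date and indication for any new antihypertensive in both groups. Count therapy towards the composite only when it was started for raised blood pressure.
3. State in advance that a donor excess in hypertension frequency will be reported without qualification only if it does not rest on the cases in (b). Otherwise report that detection cannot be separated from disease.

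The cost is one case-report field (if the full protocol does not already collect it) and one extra table; participants' care is unchanged. Two limits remain. The ambulatory limb alone misses treated hypertension, so it should not replace the composite. The indication rule removes drugs given for other reasons but not treatment prompted by closer observation, which is why both limbs need to be shown.

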#### Pulse wave velocity

Aortic PWV is the current criterion standard technique for measuring aortic stiffness.^34^ Subjects will be studied in a quiet, temperature-controlled laboratory after 15 minutes of lying supine. Pulse wave velocity (SphygmoCor; AtCor Medical, Sydney, Australia) will be determined by sequential acquisition of pressure waveforms from the carotid and femoral arteries by use of a high-fidelity micromanometer (SPC-301; Millar Instruments, Houston, TX), as previously described.^35^, ^36^ The path length will be calculated by subtracting the distance between the sternal notch and the carotid recording site from the distance between the sternal notch and the femoral site.

#### Pulse wave analysis

Blood pressure measurement will be repeated supine before undertaking applanation tonometry to record high-fidelity arterial pressure waveforms from which indices relating to large artery stiffness can be calculated. Central pressure waveforms will be derived and analyzed using the technique of pulse wave analysis, as previously described.^35^, ^37^ A micromanometer will be used to flatten but not occlude the radial artery using gentle pressure. An averaged peripheral waveform and corresponding central waveform will be generated after 11 seconds of data capture. The central waveform will then be analyzed to determine the augmentation index (the difference between the second and first peaks of the central pressure waveform, expressed as a percentage of the pulse pressure) and central aortic pressures. The method has been shown to be reproducible in both healthy subjects and in patients with CKD. Augmentation index and aPWV will also be recorded using ambulatory measurements taken from the Mobilograph.^38^, ^39^

#### Training and reproducibility

Delegated study staff will receive formal training in measurement techniques of arterial stiffness and undertake a reproducibility and measurement quality study before study commencement. Measurements at each center will only be performed by dedicated staff who have undergone this training. Equipment will be calibrated at baseline and throughout the study at specific intervals.

#### Assessment of renal function

Isotopic GFR for kidney donors will also be measured using the renal clearance of ^51^Cr-EDTA.^40^ Kidney function in controls will be estimated from serum creatinine measurement.^41^, ^42^

#### Blood and urine

Routine hematologic and biochemical parameters will be recorded, including hemoglobin, creatinine, calcium, albumin, glucose, phosphate, and PTH. A series of biomarkers will also be measured including N-terminal prohormone of brain natriuretic peptide, uric acid, urinary albumin/creatinine ratio (ACR), and fractional excretion of sodium.^43^, ^44^, ^45^

#### Long-term follow-up

Patients will also be asked to consent to longitudinal follow-up using the NHS Health & Social Care Information Centre's Data Linkage Service, which provides the patient status and tracking service to examine long-term outcomes after the study ends.

The authors are solely responsible for the design and conduct of this study, all study analyses, the drafting and editing of the manuscript, and its final contents.

## EARNEST substudies

### The Chronic Renal Impairment in Birmingham–Kidney Donor (CRIB-DONOR) study: a cardiac magnetic resonance (CMR) and echocardiography study

Those participants enrolled into the study at Queen Elizabeth Hospital Birmingham and some other centers will undergo CMR imaging and echocardiography at baseline and 12 months to determine the effects of an isolated reduction in GFR on LV mass and function as well as aortic compliance and endothelial function (online Supplementary Table I). Arterial stiffness and office and ambulatory blood pressure will also be measured at 6 months (in addition to the baseline and 12-month measurement required for EARNEST). This study is registered separately with the US National Institutes of Health database (NCT01028703) and has a current recruitment target of 140 participants.

#### Cardiac magnetic resonance imaging

Cardiac magnetic resonance imaging will be performed using a 1.5-T scanner (Magnetom Avanto; Siemens, Erlangen, Germany). Serial contiguous short-axis cines will be piloted from the vertical long-axis and horizontal long-axis images of the left and right ventricles (electrocardiogram R-wave gated, steady-state free precession imaging [True-FISP]; temporal resolution 40-50 ms, repetition time 3.2 ms, echo time 1.7 ms, flip angle 60°, slice thickness 7 mm with 3-mm gap) in accordance with previously validated methodology.^46^ Analysis will be performed offline (Argus Software; Siemens) by a single blinded observer for the assessment of ventricular volumes (end-diastolic, end-systolic and stroke volumes), function (ejection fraction), and LV mass.^46^, ^47^ In the determination of ventricular mass, volumes, and function, as compared with transthoracic echocardiography, CMR has higher interstudy reproducibility, thereby reducing the number of participants required to adequately power such studies.^48^ Aortic distensibility will be assessed at the ascending aorta and proximal descending aorta at the level of the pulmonary artery and the distal descending aorta at the level of the diaphragm on held end-expiration and calculated using previously validated formulae.^49^ Measurement of aortic distensibility using CMR has low intraobserver variability and good reproducibility.^50^ Peripheral blood pressure will be performed synchronously, in triplicate, at the brachial artery at the time of scanning for determination of pulse pressure.

Dynamic tissue-tagging MRI allows direct noninvasive assessment of regional systolic and diastolic function and is a previously validated technique.^51^ Spatial modulation of magnetization will be used to generate a uniform grid pattern with 8-mm tag separation on the LV myocardium at 3 short-axis sections (basal, mid, and apex) and the horizontal long-axis image using a fast filed echo multishot sequence (temporal resolution 40-50 ms, repetition time 3.9 ms, echo time 4.4 ms, voxel size 1.8/1.3/6.0 mm^3^, flip angel 14°, tag grid angle 45° with slice thickness 6 mm, and a minimum number of 15 phases per cardiac cycle) with prospective electrocardiogram gating, as previously described.^52^ Blinded analysis will be performed offline (CIMTag2D; University of Auckland, New Zealand) for LV strain, strain rate, and torsion calculation, as previously described.^52^

Flow-mediated dilatation of the brachial artery will also be measured using magnetic resonance measurement of brachial artery area before and after 5 minutes of arterial occlusion and also after 400-μg glyceryl trinitrate (GTN) control.^53^ Brachial artery measurements will be performed offline using semiautomated contour tracking software (MATLAB R2008b; MathWorks Inc, Natick, MA) calculating flow-mediated dilatation as the proportional change in artery diameter in response to hyperemia.^54^

